### Sample size

G*Power 3.1.9.7 was used to execute the power calculations. The change of the Cobb angle was chosen as the primary outcome indicator. Referring to the two studies from Zheng (*d* = 0.8) [59] and Liang et al. (*d* = 1.2) [60], we set the value of effect size *d* = 1.0 in our study. With a significance level of 5%, 17 subjects are needed in each group to reach a power of 80%. Allowing for a dropout rate of 15%, a total of 40 subjects will be recruited with 20 subjects for each.

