**Methods:**

The protocol describes a randomized controlled pilot trial with 40 subjects divided into study and control groups. Both groups will receive 8 weeks of PSSE, but the study group will also receive spinal manipulative therapy during the first 2 weeks before PSSE. The primary outcome will be an estimate of the feasibility of conducting a full-scale experiment. The influencing factors will be the time to complete enrollment, the recruitment rate, subject retention, and adherence to the treatment allocations. The secondary outcomes that will be used to assess the efficacy of treatment will include the Cobb angle, somatosensory evoked potentials, ATR, three-dimensional postural parameters, and scores on the 22-item Scoliosis Research Society outcomes questionnaire. The Cobb angle will be measured at baseline and at the end of 8 weeks of training. The somatosensory evoked potentials will be measured at baseline and at the end of 2 weeks of training. The ATR, three-dimensional postural parameters, and scores on the 22-item Scoliosis Research Society outcomes questionnaire will be measured at baseline and at 2 weeks, 4 weeks, and 8 weeks of treatment.

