### Assessment

Age, sex, height, weight, Risser sign, menarche status (for the girls), and type of scoliosis will be recorded at the start of the experiment. The United States Risser staging will be used to quantify skeletal maturity on a scale of 0 to 5 [43]. Stage 0 represents no ossification of the iliac apophysis, whereas stage 5 represents complete ossification and fusion. The scoliosis types will include thoracic, lumbar, thoracolumbar, and S-shaped scoliosis, corresponding to the anatomical site of the spinal deformity [1].

The primary outcome will be the feasibility of performing a full-scale study using these protocols. The time to complete enrollment, recruitment rate, subject retention, and adherence to the treatment allocation will all be important observations. The efficacy of treatment will be the secondary outcome. Spine curvature, rotation of the trunk, and postural symmetry will be assessed by the Cobb angle from X-ray images; the ATR, as measured with a Scoliometer; and 3-DPPs, as measured using a global postural system (GPS), respectively. The SEP will be assessed for evaluating sensorimotor integration, and the SRS-22 will be administered for the quality of life. The Cobb angle will be measured at baseline and at the end of 8 weeks of training. The SEP will be measured at baseline and at the end of 2 weeks of training. The ATR, 3-DPPs, and SRS-22 scores will be measured at baseline and then after 2 weeks, 4 weeks, and 8 weeks of treatment. The mean changes of Cobb angle from baseline to the end will be compared. And the mean difference of other indicators between each two visits will be used for comparative analysis.

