### Primary outcomes

The primary outcome of the study will be a judgment about the feasibility of conducting a full-scale RCT. The specific aspects of feasibility that will be monitored are listed below.

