### Interim analysis

An interim analysis will be conducted by statisticians when 20 subjects complete the experiment. In our study, the primary endpoint will be analyzed via the change of Cobb angle. In order to maintain the cumulative type I error rate at the planned 0.05, the Lan-Demets spending function method [62] with the O’Brien-Fleming spending function [63] will be used. The preplanned *P* value for stopping the trial owing to efficacy will be 0.00305. Our research team will discuss the results of the interim analysis with the ISC and the monitoring board to determine whether to stop the trial early. Besides, when a serious adverse event occurs in our study, the trial will also be terminated early.

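### Feasibility is declared the primary outcome, but the sample size and the interim efficacy stop treat the change in Cobb angle as primary

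*Protocol article*

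**What the plan says.** Feasibility as primary. The Abstract (Methods) states: "The primary outcome will be an estimate of the feasibility of conducting a full-scale experiment". The section Primary outcomes repeats it: "The primary outcome of the study will be a judgment about the feasibility of conducting a full-scale RCT". Recruitment and retention then sets numerical goals of 80% for enrolment and 80% for adherence, and the statistical analysis section has the primary measures tabulated against goals fixed in advance, with no hypothesis test.

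Cobb angle as secondary. The Abstract says: "The secondary outcomes that will be used to assess the efficacy of treatment will include the Cobb angle". The Assessment section says: "The efficacy of treatment will be the secondary outcome". The Cobb angle is the first item under the heading Secondary outcomes.

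Cobb angle as primary. The Sample size section says: "The change of the Cobb angle was chosen as the primary outcome indicator". It continues with "we set the value of effect size *d* = 1.0 in our study" and derives the 17 per group and the total of 40 from that. The Interim analysis section says: "In our study, the primary endpoint will be analyzed via the change of Cobb angle". It applies Lan-DeMets spending with an O'Brien-Fleming-type function to hold the overall error rate at 0.05, and sets P = 0.00305 for stopping on efficacy once 20 subjects have completed.

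**The concern.** The primary outcome governs what a trial is sized for, where its error control applies, what may end it early and what its conclusion rests on. Here those functions are split. The conclusion is assigned to feasibility, while sizing, error control and early stopping are assigned to a variable that the outcome sections call secondary.

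Two things are at stake. First, a reader of the final report could be shown a Cobb P value as the primary result, with the Sample size and Interim analysis sections as authority, although the outcome sections say otherwise. Second, the outcome called secondary can end the trial while the outcome called primary is still being observed. Time to complete enrolment, recruitment rate, retention and adherence are the declared primary observations, and all of them depend on the trial running to plan.

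**Working it through.** **Step 1. Which outcome do the stated figures belong to?**

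Inputs from Sample size: d = 1.0, significance level 5%, power 80%, dropout 15%. From the statistical analysis section: independent samples t test for the Cobb angle. From Randomization and blinding: 1:1 allocation. The article does not say whether the test is one- or two-sided.

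- Two-sample t test, noncentrality d × √(n/2), degrees of freedom 2n − 2, two-sided 0.05. Solving for 80% power gives n = 16.71, so 17 per group. At n = 17 the noncentrality is √8.5 = 2.92 and power is 80.7%; at n = 16 power is 78.1%. A one-sided test would give 14 per group, so the plan's 17 implies a two-sided test.
- Dropout: 17 / 0.85 = 20 per group, 40 in total. This matches the plan.
- Interim boundary: information 20/40 = 0.5. The O'Brien-Fleming-type spending function at one-sided 0.025 is 2 × [1 − Φ(z₀.₉₈₇₅ / √0.5)] = 0.001525; doubled, the two-sided nominal P is 0.00305. This matches the plan.
- The matching final two-sided nominal P is about 0.0490, and power at 17 per group is then about 80.4%, so the interim look costs almost nothing in power.

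Every figure reproduces, and every one uses a Cobb effect size or a Cobb test. None uses the feasibility goals.

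**Step 2. Does any section reconcile the labels?**

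| Section | Feasibility | Cobb angle |
|---|---|---|
| Abstract (Methods) | primary | secondary |
| Assessment | primary | secondary, as an efficacy measure |
| Primary outcomes / Secondary outcomes | primary | secondary |
| Sample size | not mentioned | primary outcome indicator |
| Interim analysis | not mentioned | primary endpoint |

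No section separates a primary feasibility outcome from a primary efficacy outcome, which would have resolved the conflict.

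**Step 3. How likely is the Cobb stop to act, and what would it cut?**

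Take 10 evaluable subjects per arm at the interim (an assumption, since simple randomization need not split evenly) and a two-sided t test at 0.00305:

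- d = 0.8 (one of the two cited studies): crossed 8.3% of the time.
- d = 1.0 (the plan's value): 16.1%.
- d = 1.2 (the other cited study): 27.5%.
- No effect: about 0.3%, by construction.

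A stop at that point comes with 20 of the planned 40 subjects completed (50%). Some further subjects will already be enrolled: at an even pace over the 24-month recruitment window given under Trial status, 40 / 24 ≈ 1.7 per month, or about 3 in the 8 weeks a subject needs to complete. Planned enrolment would then not be reached, so the time to complete it would not be observed, and adherence and retention would rest on a reduced sample.

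**The case against.** The best defence is that the Sample size section only names the variable used to size the pilot. Sizing a pilot on an efficacy variable is permissible, and if that section stood alone the wording would be a minor slip. The Interim analysis section defeats this reading: it calls the Cobb change the primary endpoint, controls type I error on it and allows a stop for efficacy on it.

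A second defence is that the boundary is not automatic, because the team is to discuss the interim result with the supervisory committee and the monitoring board before deciding. That stands and softens the risk, but nothing in the section says that the state of the feasibility data enters the decision.

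Three stronger readings are tempting and are not supported.

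- A reader might infer that the article supports either headline equally. It does not. The Abstract (Discussion) calls the efficacy data preliminary, the Background makes effect size a secondary aim, and the statistical analysis section treats the Cobb t test as one efficacy comparison among several. The ambiguity is reduced, though not removed.
- A reader might infer that the sample size or the boundary is wrong. Both reproduce. Alpha spending controls the error from repeated looks at whatever outcome it is applied to, so the boundary is valid for the Cobb angle under either label.
- A reader might add that no precision is given for the feasibility goals. That is an omission which a condensed article may leave to the full protocol or analysis plan. The exact 95% interval that could be quoted, 64% to 91%, fits only the adherence goal at exactly 32 of 40. The enrolment goal has eligible subjects as its denominator, and the interview-based parts of the primary outcome have no such interval.

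**Conclusion.** The contradiction is real and lies in the article's own statements, so an analysis plan could not resolve it without overruling one set of sections. The plan names feasibility as primary in its outcome sections and the Cobb change as primary where it sets sample size and early stopping.

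The 80% power, the 17 per group, the 40 in total and P = 0.00305 are correct but describe only the Cobb angle. The practical exposure is an efficacy stop at 20 completers. It would occur in about 16% of trials if the plan's d = 1.0 is true, and in about 8% to 27% over the two effect sizes the plan cites, assuming 10 evaluable subjects per arm and a decision that follows the boundary.

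Recruitment was under way when the article was published, so the primary outcome should be settled before the interim result is seen.

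**What to change.** Reconcile the Abstract, Assessment, Primary outcomes, Secondary outcomes, Sample size and Interim analysis sections in one of two ways.

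1. Keep feasibility as the only primary outcome. In Sample size and Interim analysis, relabel the change in Cobb angle as the main secondary (efficacy) outcome used for sizing. State that the pilot's conclusion rests on the goals under Recruitment and retention and that the Cobb comparison is preliminary.
2. Declare a primary feasibility outcome and a separate primary efficacy outcome, use those labels in every section, and say which one governs the conclusion.

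Under either option, state how the interim efficacy boundary relates to the feasibility aim. For example, make the interim Cobb result non-binding until the feasibility data are complete. Relabelling alone does not settle this, because a secondary outcome could still end a feasibility pilot at 20 completers. Stopping for safety is a separate matter and is not touched here.

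The cost is wording plus one decision about the interim rule. Sample size, test and boundary value stay as they are. Under option 1 the sponsor accepts that the 80% power and alpha-spending claims no longer describe the trial's declared primary outcome.

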### Data collection, data management, and statistical analysis

The primary outcome measures will be tabulated and interpreted with respect to the goals established a priori.

To estimate the sample size required for a future full-scale RCT, between-group effect sizes and their 95% confidence intervals will be calculated by applying Hedges’ correction. A minimum power of 80% will be used to detect changes in the Cobb angles, ATRs, 3-DPPs and SRS-22 scores (*α* = 0.05). The sample size will be increased to allow for an estimated 20% dropout rate. Statistical methods for the secondary outcome measures will be evaluated via comparisons of changes between groups.

The data will be double entered into EpiData 3.1 software (The EpiData Association, Odense, Denmark) and then transferred to version 22.0 of the SPSS software suite (IBM, Armonk, NY, USA) for the analyses. The threshold for significance will be taken as *α* ≤ 0.05. A statistician who will be blinded to the allocation results will analyze all the data. The continuous variables will be presented as means ± SDs, and the categorical variables will be presented as ratios. The baseline readings will be compared using independent samples *t* tests or chi-squared tests. For the Cobb angles and SRS-22 scores, independent samples *t* tests will be used to compare the two groups, and paired *t* tests will be used for within-group comparisons. For the M, U, MU, and M+U SEP peak amplitudes and latencies, nonparametric Wilcoxon signed-ranks tests will be used to compare these values between and within the groups. For the 3-DPPs and ATR, repeated measured analysis of variance will be used for the between-groups and within-groups comparison. Furthermore, we will perform subgroup analysis by age group (age < 13 years and age ≥ 13 years) [2, 33]. To deal with the missing data, a sensitivity analysis and weighted estimating equations will be used as the primary approach [61].

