### Randomization and blinding

The physician will explain the whole content of the trial to the candidates who meet the eligibility criteria in a separate room. Written informed consent from both subject and their statutory guardians are required. Their demographic information and medical history will then be recorded.

Each subject will be assigned to either the study or the control group using simple randomization with a 1:1 allocation. The random sequence will be generated by an investigator using an electronic random sequence generator (www.random.org). The numbers in the random sequence will be sealed in consecutively numbered, opaque envelopes. When required, the envelopes will be opened by a person who will not be involved in the intervention, assessment, or statistical analysis.

Due to the nature of the interventions, blinding of the therapists and subjects to the intervention type will be impossible, so only the assessors and those performing the statistical analysis be blinded to the allocation results. To ensure that the group allocation results remain concealed as much as possible, the assessors will process the assessments in a separate room, and the statistical analysis will not include the information about the subjects and their allocations. The schedule for the treatments and outcome assessments is presented in Fig. 2.

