#### Sample size calculation

The sample size needed for a full RCT will be estimated using the effect-size data from this pilot study.

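### The full trial's dropout allowance is preset at 20% and is not tied to the retention that the pilot observes

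*Protocol article*

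**What the plan says.** The section *Data collection, data management, and statistical analysis* describes how the full-trial size will be built. Between-group effect sizes with 95% confidence intervals come from the pilot. The power requirement is then stated: "A minimum power of 80% will be used to detect changes in the Cobb angles, ATRs, 3-DPPs and SRS-22 scores". The dropout step follows: "The sample size will be increased to allow for an estimated 20% dropout rate". No basis is given for the 20%.

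Under *Sample size calculation*, listed among the primary feasibility outcomes, the only pilot input named is the effect size: "The sample size needed for a full RCT will be estimated using the effect-size data from this pilot study".

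Retention is observed as part of the primary outcome. The *Assessment* section says: "The time to complete enrollment, recruitment rate, subject retention, and adherence to the treatment allocation will all be important observations". The goal under *Recruitment and retention* is that at least 80% of enrolled subjects attend at least 75% of sessions and complete at least 75% of the exercises.

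For the pilot itself, the *Sample size* section uses another rate: "Allowing for a dropout rate of 15%, a total of 40 subjects will be recruited with 20 subjects for each".

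**The concern.** The pilot runs the protocol that the full trial would use, so its own loss rate is a natural input to the full-trial size. The written rule takes the effect size from the pilot, although 40 subjects estimate it poorly. For dropout, which the pilot also observes, it substitutes a constant chosen before any data. If the pilot lost 30% of its subjects, the rule as written would still add an allowance for 20%.

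The 80% goal is not a full safeguard, because it measures something else. Five sessions a week for 8 weeks make 40 sessions, and 75% of 40 is 30, which is reached at the end of week 6. A subject can meet the goal and still have no week-8 Cobb angle. Weeks 5 to 8 are also the home-based part of the programme.

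What is at stake is the power of the later trial if true dropout exceeds 20%.

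**Working it through.** **Inputs from the protocol article.** Pilot: d = 1.0, significance level 5%, power 80%, 1:1 allocation, 15% dropout, 20 per group. Full trial: power at least 80%, α = 0.05, 20% dropout allowance, effect size to come from the pilot.

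**Assumptions added here.** Two-sided test (sidedness is not stated for the pilot, but two-sided reproduces its figure), full-trial d = 0.5, and a range of true dropout rates q. The document gives neither a full-trial effect size nor any dropout rate above 20%.

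**Step 1: reproduce the pilot's figure.** Two-sample t test, noncentral t, d = 1.0:
- 16 per group: 78.1% power
- 17 per group: 80.7% power

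So n = 17, as stated: "With a significance level of 5%, 17 subjects are needed in each group to reach a power of 80" percent. With 15% dropout, 17/(1 − 0.15) = 20.0 per group, 40 in total. The pilot's figures are correct.

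**Step 2: size an illustrative full trial.** At d = 0.5, 64 evaluable subjects per group give 80.1% power. With the 20% allowance, 64/(1 − 0.20) = 80 per group are enrolled.

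**Step 3: power at the true dropout rate.** Evaluable per group = 80 × (1 − q).

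| True dropout q | Evaluable per group | Power |
|---|---|---|
| 10% | 72 | 84.6% |
| 15% | 68 | 82.5% |
| 20% | 64 | 80.1% |
| 25% | 60 | 77.5% |
| 30% | 56 | 74.6% |
| 35% | 52 | 71.4% |

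**Step 4: does this depend on d = 0.5?** Hardly. In the normal approximation the effect size cancels: power = Φ[(1.960 + 0.842) × √((1 − q)/0.80) − 1.960]. This gives 82.3%, 80.0%, 77.4%, 74.6% and 71.4% at q = 15%, 20%, 25%, 30% and 35%. Solving for 75% power gives q ≈ 29.3%, so a 5-point loss needs true dropout of about 29% or more.

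**Step 5: the form of the inflation.** The sentence does not say whether the size is divided by 0.80 or multiplied by 1.2. The pilot's own step does not settle it, since 17/0.85 = 20.0 and 17 × 1.15 = 19.55 both lead to 20. With multiplication by 1.2, power at 20% dropout is about 78.4%, and the 5-point loss begins at about 26% dropout.

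**Step 6: what a pilot of 40 can exclude.** Exact (Clopper-Pearson) 95% intervals are 5.7% to 29.8% for 6/40 and 9.1% to 35.6% for 8/40. An unremarkable pilot result is therefore compatible with rates at which the fixed allowance falls short.

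**Step 7: compare allowance rules.** For each true q, the pilot's count is taken as binomial(40, q), the full trial is sized from it (64 evaluable per group, d = 0.5), and power is averaged over the possible counts.

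| True dropout | Fixed 20% | Observed proportion alone | Larger of 20% and observed |
|---|---|---|---|
| 10% | 84.6% | 80.6% | 84.6% |
| 20% | 80.1% | 80.4% | 81.5% |
| 30% | 74.6% | 80.4% | 80.5% |
| 35% | 71.4% | 80.4% | 80.4% |

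The averages for the observed proportion alone hide chance shortfalls. If true dropout is 20%, the pilot sees 15% or less with probability 0.29. An observed 15% would give 64/0.85, rounded up to 76 per group, leaving about 61 evaluable and about 78% power. The 20% floor prevents this.

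**The case against.** A reader might infer that 15% for the pilot and 20% for the full trial contradict each other, or that the difference leaves the full trial underpowered. The document does not support either reading. The rates belong to two different trials, and 20% is the more cautious. At the pilot's own 15%, the full trial would have 82.5% power, above its target.

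A reader might also infer an expected power loss of 5 points or more. That needs dropout of about 29% or higher, and the document nowhere expects more than 20%. The retention goal of 80% also agrees numerically with the 20% allowance. For week-8 loss to reach 29% with that goal met, about 9% of subjects would have to satisfy the attendance and exercise criteria and then miss the final X-ray. If those criteria cover the whole programme, that is possible but narrow.

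It can further be said that the 20% is called an estimate, that nothing bars updating it, that the later trial will need its own justification, and that a rounded allowance is ordinary practice. This stands as an argument on severity. It does not remove the point, because the article states the sizing rule, gives the number and names only the effect size as pilot input. This is a stated choice, not a detail left to a fuller document.

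Finally, relying on the observed proportion alone could lower the allowance by chance. That objection is right, and the floor in the fix answers it.

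**Conclusion.** The point holds in a limited form. The full-trial dropout allowance is a preset constant, although the pilot observes retention under the same protocol as a primary feasibility outcome. The allowance is sufficient for true dropout up to 20%, on the reading that the size is divided by 0.80. Above that, power falls by about 2.5 points below 80% at 25% dropout, 5.4 at 30% and 8.6 at 35%. These figures rest on an assumed d = 0.5, a two-sided 5% t test and dropout rates that the document does not forecast, but the effect size barely matters. Severity is minor: the planning of a later trial is affected, and the pilot's conduct, analysis and conclusions are not.

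**What to change.** In *Data collection, data management, and statistical analysis*, replace the dropout sentence with a rule of this kind: the number of evaluable subjects will be multiplied by 1/(1 − p), where p is the larger of 20% and the proportion of randomised pilot subjects without a week-8 Cobb angle; the sample size will also be reported at a stated one-sided upper confidence limit for that proportion. The confidence level should be named, because it matters. For 8/40, the one-sided exact 80% limit is 27.2% and the 95% limit is 33.2%. At d = 0.5 these give 64/(1 − 0.272) ≈ 88 and 64/(1 − 0.332) ≈ 96 per group, against 80. If another outcome is chosen as the full trial's primary measure, the proportion should be that outcome's own missing final assessments.

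The cost is one sentence and no new data. The downside is that the projected full trial may be larger: with 12/40 lost, 64/0.70, rounded up, is 92 per group instead of 80.

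### No between-group comparison uses baseline as a covariate, which costs precision, and the repeated-measures ANOVA does not say which term is the between-group test

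*Protocol article*

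**What the plan says.** Under Data collection, data management, and statistical analysis, the protocol article fixes the between-group tests by outcome. "For the Cobb angles and SRS-22 scores, independent samples" t tests are named. For the three-dimensional postural parameters (3-DPPs) and the angle of trunk rotation (ATR), "repeated measured analysis of variance will be used for the between-groups and within-groups comparison". Baseline readings are themselves compared by t or chi-squared tests, but no baseline covariate, ANCOVA or other baseline-adjusted model appears anywhere.

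The quantity compared is a change. Under Assessment: "The mean changes of Cobb angle from baseline to the end will be compared". The same section bases the other outcomes on differences between pairs of visits, and the analysis section says that secondary outcomes are judged on changes between groups. Under Sample size: "The change of the Cobb angle was chosen as the primary outcome indicator". Interim analysis also uses the change in Cobb angle.

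Cobb angle is measured at baseline and 8 weeks; ATR, 3-DPPs and SRS-22 at baseline, 2, 4 and 8 weeks. Allocation is 1:1 by simple randomization, with no stratification stated.

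**The concern.** A change score brings in baseline by subtraction, with its coefficient fixed at 1. When baseline and follow-up correlate at less than 1, that coefficient is too large. Precision is lost, and in any one sample a chance baseline difference is over-corrected. With about 34 analysable subjects and unstratified allocation, such differences will not be rare.

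For ATR and 3-DPPs, the article does not say whether baseline is a level of the time factor, or whether the group main effect or the group-by-time interaction is the between-group test. Those two terms answer different questions and can differ widely in power.

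The effect sizes matter beyond this trial. Under Primary outcomes, the largest between-group effect size selects the primary outcome of the full-scale trial, and the effect sizes set its sample size. Avoidable noise in them carries forward into that design.

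**Working it through.** **Inputs.** From Sample size: "we set the value of effect size *d* = 1.0 in our study", on the change in Cobb angle; 5% significance (two-sided reproduces the stated figure); "17 subjects are needed in each group to reach a power of 80" per cent; 15% dropout; 20 per group recruited. Assumed, because the article gives no value: baseline-to-follow-up correlation rho from 0.5 to 0.95, equal SDs at all visits and, for the ANOVA, the same correlation between every pair of visits.

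**1. The plan's own figure.** Two-sample t test, noncentral t, d = 1.0: 16 per group gives 78.1% power and 17 gives 80.7%. 17/0.85 = 20 per group, 40 in total. Both figures reproduce.

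**2. Change score against ANCOVA.** The change score has variance 2(1 − rho)SD²; ANCOVA has (1 − rho²)SD². The ratio is (1 − rho²)/[2(1 − rho)] = (1 + rho)/2. The effect size on the ANCOVA scale is 1.0/√[(1 + rho)/2], with one degree of freedom lost for the covariate. At 17 per group:

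| rho | variance ratio | CI width ratio (square root) | ANCOVA effect size | ANCOVA power |
|---|---|---|---|---|
| 0.5 | 0.75 | 0.87 | 1.155 | 90.3% |
| 0.7 | 0.85 | 0.92 | 1.085 | 86.5% |
| 0.8 | 0.90 | 0.95 | 1.054 | 84.5% |
| 0.9 | 0.95 | 0.97 | 1.026 | 82.6% |
| 0.95 | 0.975 | 0.99 | 1.013 | 81.6% |

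The change-score t test has 80.7% throughout, because d is fixed on the change scale.

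**3. Chance imbalance.** The standard error of the baseline difference is √(2/17) = 0.34 SD, so a difference beyond 0.5 SD has probability of about 14% (11% at 20 per group). Given a baseline difference b, the change-score contrast shifts by rho·b − b = −(1 − rho)b. For b = 0.5 SD this is −0.25 SD (rho 0.5), −0.15 (0.7), −0.10 (0.8) and −0.05 (0.9). ANCOVA shifts by 0.

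**4. Repeated-measures ANOVA with baseline as the first of four visits.** Take a constant effect of 0.8 SD at 2, 4 and 8 weeks and 17 per group. The 0.8 SD is illustrative; at rho 0.7 it is 0.8/√0.6 = 1.03 on the change scale, close to the planned d. At rho 0.7:

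- Group main effect: it estimates (0 + 0.8 + 0.8 + 0.8)/4 = 0.6 SD, three quarters of the effect. The variance of the four-visit mean is (1 + 3×0.7)/4 = 0.775, so the effect size is 0.6/√0.775 = 0.68 and power is 49%.
- Group-by-time interaction, 3 df: the squared deviations of (0, 0.8, 0.8, 0.8) from their mean sum to 0.48. Noncentrality is (17/2)×0.48/0.3 = 13.6 and power is 87%.
- Week-8 difference adjusted for baseline: 0.8/√(1 − 0.49) = 1.12 and power is 89%.

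In the same order, the powers are 57%, 64% and 74% at rho 0.5, and 45%, 97.2% and 96.4% at rho 0.8.

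**5. Scale of the effect size.** One change-score SD equals √[2(1 − rho)] raw SDs: 1.00, 0.77, 0.63 and 0.45 at rho 0.5, 0.7, 0.8 and 0.9. A standardised effect therefore means little unless its SD is named.

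**The case against.** The strongest defence is that the plan already accounts for baseline, because it compares changes. That stands. A reader might infer from the named t tests that imbalance goes uncorrected. That would follow if final values were compared, but Assessment, Sample size and Interim analysis all specify change for the Cobb angle. Under randomization the change-score test is unbiased, so this is a question of efficiency and of over-correction within a given sample.

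A reader might also conclude that the ANOVA definitely treats baseline as an outcome visit and tests the main effect. The visit schedule and the use of one ANOVA for both between- and within-group comparisons suggest this, but the article does not say so. Its stress on differences between visits points equally to the interaction, which does account for baseline. Against the interaction, the week-8 adjusted contrast gains about 2 points at rho 0.7 and is slightly behind at rho 0.8. The 49% therefore applies only under the main-effect reading.

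It is tempting to add that the ANOVA discards every subject with a missed visit and that the weighting model could not be fitted. The article does not establish either. It gives missing data their own approach ("weighted estimating equations will be used as the primary approach"), and nothing in it shows that approach to be unworkable.

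Finally, the declared primary outcome is feasibility, and at high rho the gain is only 1 to 2 power points. Both are true, and they limit the weight of the point. They do not remove it, since the effect sizes are a stated product of the pilot and the covariate is already collected.

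**Conclusion.** The point holds as a matter of precision and specification. No between-group analysis conditions on baseline. With d = 1.0 on change and 17 per group, ANCOVA would raise power from 80.7% to 90% at rho 0.5, falling to 82% at rho 0.95, and would narrow the confidence interval for the group difference by 13% to 1%. It would also remove a sample-specific over-correction of (1 − rho) times any baseline difference. These figures rest on an assumed rho and equal SDs. The stated sample size is correct, and ANCOVA would not increase it.

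For ATR and 3-DPPs the between-group term is undefined. The main-effect reading would lose a quarter of a constant effect and much of the power; the interaction reading would lose little. The article should say which is meant. The change is worth making because it costs almost nothing, but the present tests are not invalid.

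**What to change.** - Analyse the 8-week Cobb angle by ANCOVA, with group and baseline Cobb angle in the model.
- Analyse ATR, 3-DPPs and SRS-22 by a mixed model of the 2-, 4- and 8-week values with baseline, group, visit and group-by-visit. Name the week-8 group difference as the between-group contrast. This model uses all observed visits.
- If repeated-measures ANOVA is kept instead, state whether baseline is a level of time and which term is the between-group test.
- Derive Hedges' g from the adjusted difference and state which SD standardises it (change or raw), consistent with the planning d, which is on the change scale.
- Amend Assessment and Interim analysis, which now describe the Cobb comparison as one of mean change.

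The cost is wording only. Every covariate is already scheduled, no visit or subject is added, and the sample size need not change.
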